### Study outcomes

The primary outcome measure will be cognitive decline defined as a dichotomous variable (decline/no decline) through cognitive status criteria as described in the Assessments section below. The secondary outcomes are changes in neurocognitive scores of at least 1.5 standard deviation (SD) from baseline to endpoint (using *z* scores), a decline in the raw values of neuropsychological tests, in quality of life, functional and motor status, and falls.

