### Statistics

#### Sample size

The sample size calculation is based on two sets of data. In the LADIS observational prospective study, which included a similar population [13], there was progression in cognitive decline in 31% of the initial sample after 1 year of follow-up (200 participants out of 639 participants included). In the Osaki-Tajiri Project [72], which studied conversion to dementia in a similar population and measured different severities of cerebrovascular pathology (as in our study), odds ratios (ORs) between 2.12 and 6 were found to be implicated in the conversion into vascular dementia. We used an OR of 4 in our calculation of the expected effect (which is clinically significant).

Using Open Epi software [73] for sample calculation in randomised trials, we realised a number of 117 subjects in each arm with 95% confidence intervals (alfa of 0.05) and 80% power, giving a total of 234 subjects to be recruited. Loss to follow-up is usually 20% in this type of follow-up study, and thus a total of 280 subjects is estimated as being needed.

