#### Data analysis

Data will be registered according to the Consolidated Standards of Reporting Trials (CONSORT) guidelines for randomised controlled trials [19]. We will use intention-to-treat analyses as the primary analysis with all participants included according to initial group allocation. For the primary outcome analysis (dependent variable: cognitive decline according to clinical criteria), we will conduct a logistic regression analysis. Since the outcomes are measured at 6 and 12 months, we will fit a generalised estimating equations (GEE) logistic regression model for the data. The models will adjust for covariates which are assumed to interfere with cognition in the follow-up (age, gender, education, and baseline MoCA). For secondary outcomes, logistic or linear regression analysis will be used as applicable.

For each of the outcome endpoints (i.e. transition of cognitive status and change in neuropsychological evaluation through composite or global scores) the change from baseline to 6 months and 12 months will be assessed, even though we will consider 12 months as the primary marker of success.

Observing a statistically significant difference on any of the outcomes will be considered preliminary evidence of efficacy. We will also report variances, co-variances, and effect sizes, as well as sampling feasibility (i.e. ease of recruitment, recruitment rate, withdrawal rate).

The same qualified statistician involved in the statistical analysis designed the SAP and will independently review the analysis according to the plan.

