## Discussion

There is considerable controversy concerning the impact of physical activity on the prevention of cognitive impairment of vascular aetiology. Most of the existing evidence is garnered from observational studies, with considerable heterogeneity of methods and types of interventions. Physical activity is currently recommended for the prevention of cardiovascular diseases and is already included in the European Guidelines of Cardiovascular Prevention and Rehabilitation [11], but evidence in neurocognitive disorders is lacking. To the best of our knowledge, there are no previously published, high-quality parallel control trials on the effect of physical activity on the cognitive status of people with cognitive impairment due to cerebral vascular pathology. RCTs in other cognitive outcomes (for instance in Alzheimer’s disease) have generated controversial results [15]. In the recent DAPA trial [15], physical activity not only failed to improve cognitive status, but was associated with a mild (although not significant) cognitive deterioration. Regarding our study, we are aware of some limitations associated with the characteristics of any randomised controlled trial design, implying a selection of participants and exposure conditions that, in the end, may preclude generalisability. Nonetheless, in the absence of evidence-based interventions/treatments in vascular cognitive impairment, and considering that this is a highly prevalent pathology, we consider our study quite relevant. We believe that, in the field of neurocognitive disorders, vascular patients are more likely to benefit from physical interventions than patients with other neurodegenerative conditions. We also believe that if this study shows positive findings we will be able to deliver a simple and universal preventative treatment that can be widely disseminated in routine practice. At the same time, we are interested in determining the impact of physical activity on health-related quality of life and the motor and functional status of these patients, variables that have been understudied in this domain. Finally, we hope to explore the determinants of vascular cognitive impairment in Portuguese subjects.

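### Counting a significant result on any outcome as preliminary evidence of efficacy undercuts the single primary outcome, its 5% error rate and the 12-month marker

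*Protocol article*

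**What the plan says.** The Data analysis section of the protocol article closes its account of the models and time points with a rule for reading the results: "Observing a statistically significant difference on any of the outcomes will be considered preliminary evidence of efficacy". No outcome, visit or direction is singled out.

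Other parts of the article set a narrower standard:

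- Study outcomes names one primary outcome, cognitive decline as a yes/no variable.
- Sample size makes a single calculation, "with 95% confidence intervals (alfa of 0.05) and 80% power".
- Data analysis says that for each endpoint "the change from baseline to 6 months and 12 months will be assessed", but adds that "we will consider 12 months as the primary marker of success".

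The secondary outcomes are broad. Study outcomes lists "changes in neurocognitive scores of at least 1.5 standard deviation (SD) from baseline to endpoint", and then "a decline in the raw values of neuropsychological tests, in quality of life, functional and motor status, and falls". The sections on neuropsychological, quality of life and physical activity assessment name the individual tests and scales.

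**The concern.** A primary outcome and a primary time point are named so that one comparison, at one error rate, decides the claim. A rule that lets any outcome at any visit count as evidence of efficacy removes that protection, because every added comparison is another chance of a false positive. The 5% used to size the trial then no longer describes the risk of a mistaken efficacy statement.

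Two features make this worse. The rule speaks of a difference without giving its direction, so read literally a result favouring usual care would also qualify. The hypothesis in the Background is about cognition, yet the outcomes include motor tests such as walking distance, and the intervention is largely walking. A real fitness gain with no cognitive effect would therefore satisfy the rule, quite apart from chance.

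This is not a complaint about a missing multiplicity section, which an analysis plan could supply. The sentence is an explicit rule, and an analysis plan that confined the claim to the primary outcome would contradict it.

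**Working it through.** **Reference point.** The article gives no overall error figure to reproduce. Its only error rate is the alpha of 0.05 in Sample size. Sidedness is not stated; I take it as two-sided because it is paired with a 95% confidence interval. One test at 12 months gives 1 - 0.95^1 = 5%, of which 2.5% favours the intervention.

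**How many tests the sentence covers.** The article does not say. Three readings are possible, each at 6 and 12 months:

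1. *Narrow.* The paragraph before the rule explains its outcome endpoints, in parentheses, as transition of cognitive status and change in composite or global neuropsychological scores. That is 2 endpoints x 2 visits = 4 tests.
2. *Outcome classes.* Study outcomes lists the primary outcome, the 1.5 SD change, raw test values, quality of life, functional status, motor status and falls. That is 7 x 2 = 14 tests.
3. *Individual measures.* My count is 13 cognitive tests + 2 quality of life scales + IADL + 6 motor tests + falls = 23, and 23 x 2 = 46 tests. The primary outcome and the 1.5 SD versions are left out of this count.

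**Independent tests (upper limit).** The formula is 1 - 0.95^m for m tests:

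- m = 4: 18.5%
- m = 14: 51.2%
- m = 46: 90.6%

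These outcomes and visits are not independent, so the figures serve only as ceilings.

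**Correlated tests.** I simulated the test statistics under no effect as multivariate normal, with 100,000 draws per setting. The assumed correlation is 0.3 to 0.7 between outcomes at one visit and 0.5 to 0.7 between visits for one outcome. The correlation between different outcomes at different visits is the product of the two. A result counts if |Z| > 1.96 on any test; for differences favouring the intervention only, if Z > 1.96.

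| Reading | Tests | Either direction, two visits | Favouring intervention only, two visits | Either direction, 12 months only |
|---|---|---|---|---|
| One test at 12 months (reference) | 1 | - | 2.5% (12 months) | 5% |
| Two endpoint types | 4 | 14-17% | 7-9% | 8-10% |
| Seven outcome classes | 14 | 28-45% | 14-23% | 18-28% |
| 23 measures | 46 | 46-80% | 23-46% | 30-58% |

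The low end of each range comes from the higher correlations.

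**Reading the table.** With both visits in play, as the sentence allows, every cell is above 5%. The favourable-only column is about half the two-directional one, but its proper comparator is 2.5%, so the relative inflation is much the same: 14/5 = 2.8 and 7/2.5 = 2.8 at the low end of the narrow reading.

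**The case against.** The strongest reply is that the sentence claims little. It says preliminary evidence, not that the trial has succeeded. The primary outcome, its GEE logistic model and the 12-month marker all remain in place. The parenthesis in Data analysis also allows the narrow reading of two endpoint types, where the inflation is modest. And multiplicity among secondary outcomes is commonly left to the analysis plan.

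Much of this stands, and it limits what can be said:

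- *A false-claim risk of 40-80%, or a false claim more likely than not.* A reader might infer this by treating the outcomes as 10 to 30 independent two-sided tests (1 - 0.95^10 = 40%; 1 - 0.95^30 = 79%). The article fixes no such count, and the outcomes are correlated. A chance above one half arises only on wider counts than the narrow reading, with differences in either direction counted. Even with 23 measures it fails at a between-outcome correlation of 0.7 (46-49%), and it fails throughout the assumed range if only favourable differences count (23-46%).
- *The rule replaces the primary outcome.* It does not. It sets a looser standard beside the primary analysis.
- *The sponsor plans to roll out the treatment on any isolated result.* The Discussion does say that, with positive findings, "we will be able to deliver a simple and universal preventative treatment that can be widely disseminated in routine practice". The authors offer this as a belief, and nothing there ties it to a single secondary result.

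What the reply does not remove is the sentence itself. It refers to any of the outcomes, the preceding parenthesis does not clearly restrict it, and even the narrow reading gives 14-17%. The word preliminary lowers the strength of the claim but not how often it would be made in error.

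**Conclusion.** The sentence is wrong as written. It conflicts with the single primary outcome, the alpha of 0.05 and the 12-month marker in the same article, and it carries a false-positive chance above 5% on each of the three readings when both visits count. The size is uncertain because the article does not say how many outcomes the rule covers: about 14-17% on the narrow reading, 28-45% for seven outcome classes, 46-80% for about 23 measures, and roughly half of each if only differences favouring the intervention count.

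The figures rest on assumed correlations, on my own count of measures and on a separate test at each visit. The direction of the conclusion depends on none of these, only on more than one comparison being allowed to count. One narrower case should be noted: two endpoint types, 12 months only and favourable differences only would give about 4-5%, half of the 8-10% in the table. That is below 5% but still above the 2.5% of a single test, and the sentence does not contain those restrictions.

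**What to change.** Replace the sentence in Data analysis with:

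*Efficacy will be concluded only from the primary outcome at 12 months (two-sided 5%), in favour of the intervention. Secondary outcomes and 6-month results are supportive and will be reported as estimates with 95% confidence intervals.*

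This brings the false-positive rate back to that of one two-sided 5% test. It needs no change to data collection, visits or sample size. The cost is that the sponsor can no longer claim efficacy from an isolated secondary or 6-month result.

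Keeping every outcome class in the rule would instead need an explicit adjustment. For 14 tests, Bonferroni gives 0.05/14 = 0.0036 per test. A formal testing order for a short list of secondary outcomes is optional and not needed to correct the defect.

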## Discussion

There is considerable controversy concerning the impact of physical activity on the prevention of cognitive impairment of vascular aetiology. Most of the existing evidence is garnered from observational studies, with considerable heterogeneity of methods and types of interventions. Physical activity is currently recommended for the prevention of cardiovascular diseases and is already included in the European Guidelines of Cardiovascular Prevention and Rehabilitation [11], but evidence in neurocognitive disorders is lacking. To the best of our knowledge, there are no previously published, high-quality parallel control trials on the effect of physical activity on the cognitive status of people with cognitive impairment due to cerebral vascular pathology. RCTs in other cognitive outcomes (for instance in Alzheimer’s disease) have generated controversial results [15]. In the recent DAPA trial [15], physical activity not only failed to improve cognitive status, but was associated with a mild (although not significant) cognitive deterioration. Regarding our study, we are aware of some limitations associated with the characteristics of any randomised controlled trial design, implying a selection of participants and exposure conditions that, in the end, may preclude generalisability. Nonetheless, in the absence of evidence-based interventions/treatments in vascular cognitive impairment, and considering that this is a highly prevalent pathology, we consider our study quite relevant. We believe that, in the field of neurocognitive disorders, vascular patients are more likely to benefit from physical interventions than patients with other neurodegenerative conditions. We also believe that if this study shows positive findings we will be able to deliver a simple and universal preventative treatment that can be widely disseminated in routine practice. At the same time, we are interested in determining the impact of physical activity on health-related quality of life and the motor and functional status of these patients, variables that have been understudied in this domain. Finally, we hope to explore the determinants of vascular cognitive impairment in Portuguese subjects.
